## Abstract

**Background:**

Treatment standard for patients with atypical or anaplastic meningioma is neurosurgical resection. With this approach, local control ranges between 50% and 70%, depending on resection status. A series or smaller studies has shown that postoperative radiotherapy in this patient population can increase progression-free survival, which translates into increased overall survival. However, meningiomas are known to be radioresistant tumors, and radiation doses of 60 Gy or higher have been shown to be necessary for tumor control.

Carbon ions offer physical and biological characteristics. Due to their inverted dose profile and the high local dose deposition within the Bragg peak precise dose application and sparing of normal tissue is possible. Moreover, in comparison to photons, carbon ions offer an increased relative biological effectiveness (RBE), which can be calculated between 2 and 5 depending on the cell line as well as the endpoint analyzed.

First data obtained within the Phase I/II trial performed at GSI in Darmstadt on carbon ion radiotherapy for patients with high-risk meningiomas has shown safety, and treatment results are promising.

**Methods/design:**

The Phase II-MARCIE-Study will evaluate a carbon ion boost applied to the macroscopic tumor in conjunction with photon radiotherapy in patients with atypical menigiomas after incomplete resection or biopsy.

Primary endpoint is progression-free survival, secondary endpoints are overall survival, safety and toxicity.

**Discussion:**

Based on published data on the treatment of atypical meningiomas with carbon ions at GSI, the present study will evaluate this treatment concept in a larger patient population and will compare outcome to current standard photon treatment.

**Trial registration:**

NCT01166321

## Background

Meningiomas are the second most common primary brain tumor and represent approximately 15-26% of all intracranial neoplasms [1]. Approximately 5-10% of meningiomas are of non-benign histology (atypical or anaplastic) and are associated with less favourable outcome; they are characterized by locally aggressive growth and early recurrence or tumor progression after surgery [2]. Therefore, neurosurgical resection alone does not confer to high long-term local control and overall survival rates [3]. Moreover, extent of tumor resection has shown to be a significant prognostic factor. The resection level is commonly assessed after neurosurgical resection by the surgeon after verification with a postoperative MRI and is classified according to Simpson guidelines (see table 1).

**Table 1 T1:** Simpson grading for Meningioma

Radical	
**Stage 1**	complete excision, including dura and bone
**Stage 2**	complete excision + supposed reliable coagulation of dural attachment.
**Non-radical**	
**Stage 3**	complete excision but insufficient dural coagulation or bone excision (non visible on MR, according to surgeon's opinion)
**Stage 4**	incomplete excision, macroscopic rest visible (on MRI)
**Stage 5**	biopsy only (visible on MRI)

Patients after non-radical resection (Simpson Grade 4 and 5) show significantly worse outcome than patients after radical neurosurgical resection [4]: In patients with non-bening meningiomas treated with surgery alone, local recurrence rates are 50% for subtotally excised, and 90% for completely resected patients at 3 years as reported in a large multi-center overview. Local recurrence has a major negative impact on survival.

Although meningiomas are classified as relatively radioresistant tumors, radiation therapy is the most effective adjuvant treatment available [5-8]. For non-benign meningiomas, a number of small and non- controlled series have reported superior outcome after postoperative radiotherapy as compared to surgery alone [6,9-13].

Novel radiotherapeutic modalities such as protons or carbon ion radiotherapy offer a promising treatment alternative. Radiation therapy using charged particles is characterized by distinct physical and biological characteristics. Charged particles provide the physical advantage of an inverted dose profile which enables steep dose gradients. Therefore, reduction of dose to normal tissue, and especially to organs at risk, can be achieved. Heavy charged particles, such as carbon ions, additionally offer an increased RBE. Thus, with particle therapy, dose escalation required for long-term control of atypical or malignant meningiomas is feasible while adhering to normal tissue tolerance constraints. New beam qualilties, such as carbon ion radiation therapy, offer a promising treatment alternative in malignant meningiomas. Carbon ion radiotherapy offers the physical characteristics as do protons, however, are characterized by a comparably higher RBE. For aggressive and radioresistant tumors auch as glioblastoma cell lines, RBE values between 2 and 5 have been reported depending on cell line and endpoint [14,15]. Clinically, it has been shown that carbon ion radiation therapy leads to significantly increased control rates in treatment-resistant tumors [16-18].

Carbon ion radiotherapy was available by the Department of Radiation Oncology at GSI in Darmstadt since 1997. Superior treatment results for a number of tumor entities, such as chordomas and chondrosarcomas of the skull base, as well as ACC have been shown, and carbon ion radiotherapy is currently performed in the clinical routine for these patients [17,18]. Safety of carbon ion radiotherapy with respect to critical organs at risk, such as the brain, brainstem or spinal chord, have been shown in these studies. At the HIT center, treatment of over 1300 patients per year with Proton and Carbon ion RT is possible. Worldwide, particle therapy is available in the clinical routine in a few of centers until now.

Over recent years, a number of centers have implemented proton radiotherapy for patients with meningiomas, mainly with benign histology. Results are summarized in table 2.

**Table 2 T2:** Results of Proton and Carbon Ion Therapy for Patients with Meningiomas

Author	Institute	Year	No. of Pts.	Radiation Modality	Overall Survival	Local Control
Austin-Seymour et al.	MGH, Boston MA, USA	1990	13	Protons, 59,4 Gy E	100%	100%
Gudjonsson et al.	Uppsala, Sweden	1999	19	Protons, 24 Gy E, 4 fractions	-	100% at 3 years
Wenkel et al.	MGH, Boston MA, USA	2000	46	Protons and Photons, 59.0 Gy E	95% and 77% at 5 and 10 years	100% and 88% at 5 and 10 years
Hug et al.	MGH, Boston MA, USA	2000	16	Protons and Photons, 62 Gy E for atypical meningiomas, 58 Gy E for malignant meningiomas	-	19% at 8 years for atypical meningiomas, 17% at 8 years for malignant meningiomas
Vernimmen et al.	Tygerberg, South Africa	2001	27	Protons, 54 Gy E - 61.6 Gy E, 16 - 27 fractions	-	88%
Noël et al.	CPO, Orsay, France	2002	17	Protons and Photons, 61 Gy E	88.9% at 4 years	87.5% at 4 years
Weber et al.	PSI, Switzerland	2004	16	Protons, 52.2-64 Gy E	92.7% at 3 years	91.7% at 3 years
Noël et al.	CPO, Orsay, France	2005	51	Protons and Photons, 60.6 Gy E	100% at 4 years	98% at 4 years
Combs et al.	Heidelberg, Germany	2010	10	Photons, Carbon Ion Boost	75% and 63% at 5 and 7 years	86% and 72% at 5 and 7 years

Outcome after proton as well as advanced photon radiotherapy are comparable for the treatment of benign meningiomas, with high local control rates and low rates of treatment-related morbidity. However, for benign meningiomas, total doses of 50 to 60 Gy are required for long-term tumor control. For anaplastic and atypical meningiomas, on the other hand, doses of 60 Gy are known to be not sufficient for long-term tumor control, and possibilities of dose-escalation play an important role for the improvement of outcome. Smaller studies could show that total doses exceeding 60Gy are required for long-term tumor control [13,19]. Therefore, until now, distinctly worse clinical results are still observed observed in WHO Grade II and III meningiomas. Atyical and anaplastic meningiomas remain a difficult to treat patient population with high rates of local tumor recurrences, even after aggressive surgery and adjuvant radiation therapy.

Preliminary results obtained after carbon ion radiotherapy within a Phase I/II trial performed at GSI could show safety and feasibility in patient with high-risk meningiomas treated with a carbon ion boost to the macroscopic tumor in combination with precision photon radiotherapy delivered as IMRT or FSRT [20]. These patients had been treated in our institution within a dose of 50.4 Gy with photons delivered by FSRT or IMRT, and a carbon ion boost to the macroscopic tumor with a total dose of 18Gy E in single doses of 3 Gy E [20]. No severe acute or long-term toxicity could be observed, and treatment outcome with with overall survival rates of 75% and 63% at 5 and 7 years is promising, although all patients had macroscopic tumors at the timepoint of radiotherapy. Therefore, the concept of a carbon ion boost to patients with atypical meningiomas with a macroscopic tumor lesion after neurosurgical resection is a promising treatment alternative.

In the present MARCIE trial, impact of a carbon ion boost using intensity modulated rasterscanning delivered in combination with precision photon radiotherapy will be evaluated in a Phase II design in patients with atypical meningiomas.

## Methods and Design

The purpose of the trial is to evaluate a carbon ion boost to the macroscopic tumor in combination with photon radiotherapy in patients atypical meningiomas.

The aim of the study is to compare progression-free survival as a primary endpoint, and overall survival free survival, toxicity and safety as secondary endpoints.

The primary objective is progression-free survival rate during the follow-up phase of at least 3 years. The secondary objectives of the study are overall survival, toxicity and safety.

The trial will be performed as a single-center one-armed Phase II study.

Patients fulfilling the inclusion criteria will be included.

### Treatment Schedule

Carbon Ion Radiation Therapy as a Boost to the macroscopic tumor

Total Dose 18 Gy E, 6 fractions, 3 Gy E single dose

The trial workflow is shown in Figure 1.

**Figure 1 F1:**
[figure not shown]
**Flow chart of the MARCIE-Study**.

### Study objectives and endpoints

The primary endpoint is progression-free survival at 3 years, therefore patients are followed within the trial protocol for a minimum 3 years after completion of study treatment. For the LPI (last patient in), the final study visit will be 3 years after study treatment to asses the primary endpoint. All other patients will be followed on a regular basis as stated below until death or until 3 years after LPI.

After RT, patients are scheduled for follow-up visits every 3 months or as needed clinically including contrast-enhanced MRI as well as thorough clinical-neurological assessment.

The last patient included into the study will be followed 3 years after treatment. This is considered the final study visit. All other patients will be followed regularly as described in detail until death or until 3 years after LPI.

The overall duration of the trial is expected to be approximately 72 months. Recruitment of the patients is planned over a time period of 36 months, minimum duration of the follow-up phase will be 36 months.

### Patient selection

40 patients should be enrolled in this clinical study fulfilling the following inclusion criteria.

### Inclusion criteria

Patients meeting all of the following criteria will be considered for admission to the trial:

- histologically confirmed atypical meningioma

- macroscopic tumor after biopsy or subtotal resection - Simpson Grade 4 or 5

- prior photon radiotherapy to the CTV_Photon _of 48-52 Gy

- beginning of study treatment no later than 12 weeks after surgery

- age ≥ 18 years of age

- Karnofsky Performance Score ≥60

- For women with childbearing potential, adequate contraception.

- Ability of subject to understand character and individual consequences of the clinical trial

- Written informed consent (must be available before enrolment in the trial)

### Exclusion criteria

Patients presenting with any of the following criteria will not be included in the trial:

- refusal of the patients to take part in the study

- previous radiotherapy of the brain

- time interval of >12 weeks after primary diagnosis (neurosurgical intervention) and beginning of study treatment

- optic nerve sheath meningioma (ONSM)

- Patients who have not yet recovered from acute toxicities of prior therapies

- Known carcinoma <5 years ago (excluding Carcinoma in situ of the cervix, basal cell carcinoma, squamous cell carcinoma of the skin) requiring immediate treatment interfering with study therapy

- Pregnant or lactating women

- Participation in another clinical study or observation period of competing trials, respectively.

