### Treatment Planning

For radiotherapy, patients will be immobilized using an individually manufactured head mask. For treatment planning, contrast-enhanced CT as well as MR-imaging will be performed for optimal target definition.

Organs at risk such as the brain stem, optic nerves, chiasm and spinal chord will be contoured. Dose constraints of normal tissue will be respected according to Emami et al. [21].

The carbon ion boost will consist of the GTV including the area of contrast enhancement on T1-weighted MR-imaging; the CTV_Carbon _for the boost will be defined adding a safety margin of 5 mm.

Amino-Acid-PET or ^68^Ga-Dotatoc-PET may be used in addition to contrast-enhanced MRI for target volume definition but is not mandatory.

For photon treatment, the CTV_Photon _will be defined, which is applied as 3D-conformal treatment or as high-precision photon radiotherapy such as FSRT or IMRT. The CTV_Photon _will be contured including the GTV and sub clinical microscopic tumor (e.g. including the pre-operative tumor or post-operative tumor bed, peritumoral edema, hyperostotic changes if any, and dural enhancement or thickening as seen in the CT/MRI at diagnosis) plus a 1 cm safety margin. The margin may be reduced with respect to anatomical borders or organs at risk at the discretion of the investigator. Treatment Planning for Photon Radiotherapy will be performed using the Planning Systems available at the Department of Radiation Oncology in Heidelberg, Germany (including HELAX-Masterplan/Nucletron, Virtuos-Konrad/Siemens, or STP/Stryker-Leibinger).

Carbon ion RT planning is performed using the treatment planning software PT-Planning (Siemens, Erlangen, Germany) including biologic plan optimization. Biologically effective dose distributions will be calculated using the a/ß ratio for meningioma as well as for the endpoint late toxicity to the brain.

No interruptions >4 days between the end of photon radiotherapy and the carbon ion boost are allowed.

Patient positioning prior to radiotherapy will be evaluated by comparison of x-rays to the DRRs. Set up deviations >3 mm are corrected prior to radiotherapy.

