### - Progression-free Survival -

Progression-free survival is the primary endpoint of the study. Progression-free survival will be counted from the first day of radiotherapy treatment until the date of the first event of either progression or death due to any cause. Patients alive without progressive disease at the time of data analysis will be censored at the time of the most recent follow-up visit.

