### Statistical Methods

#### Confirmatory Analysis

The primary aim and its corresponding endpoint are subject to a confirmatory statistical analysis. The primary aim is to evaluate efficacy of carbon ion boost in combination with postoperative photon radiotherapy in patients with atypical meningiomas Simpson grade 4 and 5 on progression-free survival rate after 3 years of follow-up (PFS-3yR). Formally,

H_0_: PFS-3yR ≤ 0.5 versus H_1_: PFS-3yR > 0.5.

PFS-3yR is statistically tested with a one-sided binominal test on the level α = 5%.

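### The protocol conflicts with itself on whether the 48-52 Gy photon course is prior therapy or trial treatment; read literally, toxicity of the combined regimen could be understated

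*Protocol article*

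**What the plan says.** All references are to the protocol article.

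Text that treats the photon course as something before the trial treatment:
- Inclusion criteria require "prior photon radiotherapy to the CTV_Photon _of 48-52 Gy".
- Treatment Schedule names one treatment: "Carbon Ion Radiation Therapy as a Boost to the macroscopic tumor". No photon course is listed there.
- Exclusion criteria bar "Patients who have not yet recovered from acute toxicities of prior therapies", without naming the therapies, a toxicity grade or a time point.

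Text that treats it as part of the trial course:
- Exclusion criteria also bar "previous radiotherapy of the brain".
- Treatment Planning defines the photon target volume and planning systems prospectively, and states: "No interruptions >4 days between the end of photon radiotherapy and the carbon ion boost are allowed".
- The endpoint definition says: "Progression-free survival will be counted from the first day of radiotherapy treatment". It does not say whether this means photons or boost.
- Study Hypothesis and Confirmatory Analysis concern the combination; the latter aims to "evaluate efficacy of carbon ion boost in combination with postoperative photon radiotherapy".

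The analysis sets add to this. Full Analysis Population leaves out patients later found to have breached major entry criteria. Safety Population is the part of that set that received study treatment at least once. Follow-up ties the toxicity evaluation to study treatment. Descriptive Analysis counts how many patients had treatment as planned, late or stopped for good.

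**The concern.** Toxicity and safety are secondary endpoints, and the regimen under test is photons plus boost. If eligibility is judged after the photons and the photons count as a prior therapy, the trial admits only patients who reached 48-52 Gy and have recovered from its acute effects, with at most 4 days in which to do so. Patients who stopped photons early, or were unfit at their end, would then be absent from the toxicity table and from the tolerability counts. A safety statement about the combination would rest on those who had already come through its first part.

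The article does not settle whether that is what is meant. Two investigators could apply the criteria differently and both claim compliance, and the toxicity denominator would differ between them.

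**Working it through.** **1. Is there a figure to reproduce?** No. The article prints no acute toxicity rate and no rate of failing to proceed from photons to boost. The check is therefore of wording first, and of size only by illustration.

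**2. Three readings against the stated rules.**

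| Reading | Consequence for entry and safety set | Stated rule it collides with |
|---|---|---|
| A. Photons are prior therapy, the toxicity exclusion covers them, eligibility is judged after them, study treatment is the boost | Entry depends on completing photons and on recovering from them; the safety set starts at the boost | The bar on earlier brain radiotherapy, which taken literally would exclude everyone the inclusion criterion requires |
| B. Eligibility is judged after photons, but the toxicity exclusion means surgery only | The toxicity exclusion selects nobody on photon tolerance; the 48-52 Gy criterion still leaves out patients who stop photons early | The same bar on earlier brain radiotherapy |
| C. Enrolment precedes photons, and photons are study treatment | No selection on photon tolerance | The inclusion criterion, which calls the photons prior, and Treatment Schedule, which lists the boost alone |

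No reading satisfies every sentence. The conflict is therefore in the text itself.

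**3. How the selection would carry through under A.** Safety Population requires (i) membership of the full analysis set and (ii) at least one study treatment. Under A, (ii) means at least one boost fraction. A patient who starts photons but is unfit for the boost fails (ii). A patient treated despite unresolved photon toxicity could fail (i), if that exclusion is regarded as a major criterion. Both are lost from the toxicity denominator.

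**4. Size: illustration only.** Let a be the share of patients with photon toxicity unresolved when the boost is due, and b the share with toxicity on the boost. Assume that the two are independent, every affected patient is screened out, and photon-phase events go uncounted. Then:

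- whole-regimen rate = 1 − (1 − a)(1 − b)
- reported rate = b

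With b = 5% assumed:
- a = 5%: 1 − 0.95 × 0.95 = 9.75%
- a = 10%: 1 − 0.90 × 0.95 = 14.5%
- a = 20%: 1 − 0.80 × 0.95 = 24.0%

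The reported rate is 5% in each case. Neither a nor b comes from the article. Under B with no early stopping, or under C, the shortfall from this mechanism is zero.

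**5. What the article's own toxicity evidence can add.** Background reports no severe acute or long-term toxicity in the earlier series of 50.4 Gy photons plus the same 18 Gy E boost, and Table 2 gives 10 patients. With 0 events in 10, the one-sided 95% upper limit is 1 − 0.05^(1/10) = 1 − 0.741 = 25.9%. The series neither supports a high rate nor rules one out. With 40 patients planned, each patient is 1/40 = 2.5 percentage points, so a few missing patients would show in the table.

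**The case against.** The strongest reply is that the exclusion list makes sense only if the protocol photon course is not counted as earlier treatment, because otherwise nobody could be enrolled. The toxicity exclusion then most naturally refers to surgery or other earlier treatment, and the mechanism disappears. Prospective photon planning, the PFS origin and the benchmark population in Study Hypothesis (no previous radiotherapy) fit that view. This stands as evidence for the benign reading. It does not remove the inclusion criterion that calls the photons prior, nor the boost-only Treatment Schedule.

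A second reply is that the bias argument needs two readings at once. If study treatment is the boost, patients who never reach it are not missing from a boost safety set; if it is the combined course, the photons are not prior. This is right as far as it goes. The difficulty arises when a safety set built on the boost supports a statement about the combination, and the article's wording permits that because its hypothesis names the combination.

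Third, enrolment timing and the adverse-event window may be in the full protocol, or in Figure 1, which is not shown. Their absence from the article is no finding; the conflict between rules that the article does state is.

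A reader might go further and infer that entry does select patients who tolerated the photons, that regimen toxicity is understated as a fact, or that the PFS cohort is enriched. The documents do not support this: the first two depend on reading A (or, in part, B), and nothing quantifies a PFS effect. Nor do they establish that any acute reaction lasting beyond 4 days bars a patient. The exclusion sets no grade or time point, and the 4-day limit is a delivery rule under Treatment Planning, not an entry criterion.

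**Conclusion.** The point holds as a conflict between stated rules with a conditional consequence. Treatment Schedule, the inclusion and exclusion criteria, Treatment Planning and the PFS definition cannot all be followed as written, because they disagree on whether the photon course is prior therapy or trial treatment. On the literal reading, entry and the safety set are conditional on completing and tolerating the photons, and toxicity and tolerability of the combined regimen could be understated. If the toxicity exclusion refers to surgery only, it causes no such selection, but early photon stoppers are still left out if eligibility is judged after the photons. If enrolment precedes the photons and they are study treatment, this mechanism produces no bias.

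The direction is clear under the literal reading; the size cannot be computed from the article. The percentages in the working rest wholly on assumed rates and should not be quoted as estimates. The matter should be put right because it determines the denominator of a secondary endpoint. It is not shown to alter the primary test.

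**What to change.** 1. Reconcile the sections named above. State whether the photon course is prior therapy or study treatment, when enrolment occurs relative to it, and whether the toxicity exclusion includes it. Say which radiotherapy the PFS start date refers to. Which clinical rule applies is for the sponsor; none is proposed here.
2. Report CTCAE toxicity and tolerability from the first photon fraction for every consented patient who starts photons, including those who never start the boost, with the reason.
3. If only toxicity of the boost is intended, say so, and limit the safety conclusion to patients who completed the photons.

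Cost: an amendment to the wording, and CTCAE recording during the photon course. The article gives no photon fraction size. Assuming 1.8-2 Gy on five days a week, the course lasts from 48/2/5 = 4.8 to 52/1.8/5 = 5.8 weeks. The trial is single-center and photon planning uses the same department's systems, so the added work is modest. Consent would have to be in place before photons start. Reported toxicity may look less favourable.
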